**Study objectives**

Primary objective

To compare the effects of continuous blue light exposure during driving with those of coffee (2*200 mg of caffeine) and coffee placebo on 4h night-time driving performance in young (20-25 years) and middle-aged (40-50 years) healthy volunteers

Secondary objectives

To determine the effect of age in the effectiveness of countermeasures (blue light and coffee)

To determine individual differences (cognitive, genetic and hormonal) in the impairment of neurobehavioral functions from sleep loss and in the effectiveness of countermeasures (blue light and coffee)

To determine the effects of blue light on quality and quantity of sleep after night-time driving in young and middle-aged healthy volunteers

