**Statistical considerations**

Determination of sample size

The sample size calculation (G power software) was done in order to allow demonstrating a slight difference between the 2 countermeasures (coffee and blue light) with a power of 90 % and a type-I error =5% approximately 48 subjects have to be included in the study:

Effect size f = 0.3

α err prob = 0.05

Power (1-β err prob) = 0.9

Total sample size: 48 **(24 young and 24 middle-aged)**

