**Analyses of variables**

Analysis of primary efficacy variable

The results will be analyzed by using negative binomial regres­sion in Stata, version 8.0 (Stata Corp., College Station, Texas), using number of ILC per participant as dependent variables and treatments (Blue light, coffee, or placebo), age or type as determi­nants clustered on participants. We reported comparisons of ILC between treatments as incidence rate ratios (IRR) with 95% confi­dence intervals (CI). Where binomial negative regression are not possible because there are no line crossing, the Wilcoxon non­parametric test will be used.

Analysis of secondary efficacy variables

The standard deviation of the position of the car will be compared by a two-way analysis of variance (ANOVA) (age*treatment, genotype*treatment, hormonal type *treatment, cognitive type*treatment, …).

Subjective sleepiness or subjective fatigue will be compared by a three-way analysis of variance for repeated measurements (rANOVA) (time*age*treatment, time*genotype*treatment, time*hormonal type*treatment, time*cognitive type*treatment, …)

Sleep latency, sleep efficiency or sleep EEG power density will be compared by a three-way analysis of variance for repeated measurements (rANOVA) (time*age*treatment, time*genotype*treatment, time*hormonal type*treatment, time*cognitive type*treatment, …).

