**Expected results**

- Improvement of nocturnal driving ability with countermeasures to sleepiness (coffee and continue blue light exposure) versus placebo in young and middle-aged healthy volunteers.

- Same beneficial effect of continue blue light exposure versus coffee on nocturnal driving ability in young and middle-aged healthy volunteers.

- Characterization of biological (genetic, cognitive or hormonal) markers explaining inter-individual variability in nocturnal driving impairment and effectiveness of countermeasures to sleepiness.

- Modifications on quality and quantity of sleep after the blue light exposure during nighttime driving in young and middle-aged healthy volunteers.

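### The line-crossing model gives each marker, or age, one coefficient over all three nights, so it cannot separate vulnerability to sleep loss from response to a countermeasure

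*Protocol*

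**What the plan says.** The protocol's secondary objectives (Study objectives) put three questions about subgroups. The first is whether age alters the effectiveness of blue light and coffee. The next objective has two halves. One half is "To determine individual differences (cognitive, genetic and hormonal) in the impairment of neurobehavioral functions from sleep loss"; the other is individual differences in how well the countermeasures work. The Expected results section promises both halves together: "Characterization of biological (genetic, cognitive or hormonal) markers explaining inter-individual variability in nocturnal driving impairment and effectiveness of countermeasures to sleepiness".

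For ILC, the section Analyses of variables gives one negative binomial regression with "treatments (Blue light, coffee, or placebo), age or type as" determinants, clustered on participants. Treatment comparisons are to be reported as IRRs with 95% confidence intervals. No product of age or type with treatment is written, and no night is singled out for the impairment question.

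Further down in the same section, lateral position is to be analysed with "age*treatment, genotype*treatment, hormonal type *treatment, cognitive type*treatment". Sleepiness, fatigue and the sleep outcomes get the corresponding three-way terms with time.

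Under Study design, each participant drives three nights: blue light, caffeine and caffeine placebo. No rested reference drive is described. Under Treatment, the placebo drink contains 15 mg of caffeine.

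**The concern.** A model with treatment and type as main effects assumes that the marker multiplies the ILC rate by the same factor on every night. Two problems follow.

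- It has no parameter for a difference in countermeasure effect between age or marker groups. The age objective and the effectiveness half of the marker objective therefore cannot be answered for the primary criterion.
- Its one type coefficient averages one night without an active countermeasure and two nights with one. If the marker effect differs between nights, that coefficient is neither the vulnerability effect nor the response effect.

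The protocol itself expects such differences. It says that the effect of caffeine varies between individuals, lists caffeine sensitivity and the ADORA2A polymorphism among its criteria, and expects both countermeasures to improve driving. A marker of caffeine response could then be reported as a marker of vulnerability to sleep loss. A vulnerability marker whose effect the countermeasures weaken could be missed.

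**Working it through.** **1. The plan's own figure.** Statistical considerations gives "Effect size f = 0.3", "α err prob = 0.05", "Power (1-β err prob) = 0.9" and "Total sample size: 48". The test family and the within-person correlation are not stated. For a within-subject ANOVA over m = 3 nights with correlation ρ = 0 (assumed), the noncentrality is λ = f²·N·m/(1−ρ) = 0.09 × 48 × 3 = 12.96, and power at N = 48 is 0.897; power of 0.90 needs N = 49 or 50. So 48 is reproduced closely under that reading. It is not reproduced with ρ = 0.5 (N = 25–26). The figure is for coffee against blue light; no marker or age effect is sized.

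**2. What the single coefficient estimates.** Let b_P, b_C and b_B be the marker's log IRR on the placebo, coffee and blue-light nights. With strong overdispersion the nights carry nearly equal weight, so the pooled IRR ≈ exp[(b_P + b_C + b_B)/3]:

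- IRR 2.0 on the placebo night only: 2^(1/3) = 1.26.
- IRR 2.0 on the coffee night only: 2^(1/3) = 1.26, the same value from the opposite cause.
- IRR 3.0 on the coffee night only: 3^(1/3) = 1.44.
- IRR 2.0 on placebo and half the log effect on the other nights: (2 × √2 × √2)^(1/3) = 4^(1/3) = 1.59.
- IRR 2.0 on all nights: 2.0.

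With little overdispersion the weights approach the mean counts, and the pooled IRR approaches the ratio of totals. For assumed means of 10/4/4 (placebo/coffee/blue light), a placebo-only IRR of 2.0 gives (20+4+4)/(10+4+4) = 28/18 = 1.56, and a coffee-only IRR of 2.0 gives (10+8+4)/18 = 22/18 = 1.22. The weights change, but the mixing remains.

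**3. Simulation of the stated model.** Assumptions, none of them in the protocol: half of the 48 participants carry the marker; between-person SD 0.6 on the log scale; dispersion 0.5; mean ILC of 10/4/4, 10/5/5, 10/7/7 or 20/5/10. There were 600 runs per setting, so the Monte Carlo standard error is at most √(0.25/600) ≈ 2 points. Ranges are over the four sets of means.

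| True marker IRR (placebo/coffee/blue light) | Pooled IRR | Pooled rejection | Placebo-night IRR | Placebo-night rejection |
|---|---|---|---|---|
| 1 / 1 / 1 | about 1.0 | 7–9% | about 1.0 | 7–10% |
| 2 / 1 / 1 | 1.26–1.28 | 19–23% | about 2.0 | about 65% |
| 2 / √2 / √2 | 1.58–1.63 | 52–58% | about 2.0 | 65–70% |
| 2 / 2 / 2 | about 2.0 | 84–86% | about 2.0 | 64–68% |
| 1 / 2 / 1 | 1.24–1.28 | 18–21% | about 1.0 | 7–10% |
| 1 / 3 / 1 | 1.42–1.43 | 36–37% | about 1.0 | 7–8% |

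The first row shows that the clustered test already rejects somewhat above 5% at this sample size. The rates in the last two rows should be read against 7–10%.

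**4. Price of using one night.** For a continuous outcome with unit SD per night and between-night correlation ρ, the SD of a three-night mean is √((1+2ρ)/3) = 0.730, 0.816 and 0.894 for ρ = 0.3, 0.5 and 0.7. The placebo-night standard error is larger by the factor 1/0.730 = 1.37, 1/0.816 = 1.22 or 1/0.894 = 1.12.

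**The case against.** The protocol never says that a marker main effect will be read as impairment. It only lists determinants, and the one quantity it promises to report is the treatment comparison. The choice of contrast for a secondary objective is commonly left to an analysis plan, which is not at hand. This stands in part: the pooling is read from the list of terms, not declared. But the protocol does fix the terms of the ILC model, and its neighbouring paragraphs write the interactions out, so main effects only is the natural reading. No choice of contrast recovers a night-specific marker effect from a model without the interaction.

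A reader might extend the point to lateral position, sleepiness, fatigue and sleep. The document does not support that. Those models contain the marker-by-treatment terms, so the placebo-night effect can be obtained from them, and nothing says that the analyst will ignore the interaction.

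A reader might also infer that pooling always dilutes a vulnerability marker. It does not. Equal effects on all nights leave the coefficient unbiased and raise power (84–86% against 64–68%). With half the log effect on the treated nights the loss is moderate (52–58% against 65–70%). The protocol expects the countermeasures to improve driving, not to abolish marker effects.

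Finally, the placebo night is not a clean reference. It carries 15 mg of caffeine per drink. Without a rested drive it shows the level of driving under sleep loss, not the change that sleep loss causes. Its error also enters both the impairment contrast and, with opposite sign, the effectiveness contrasts. All of this stands and limits what the fix can claim.

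**Conclusion.** The point holds for the ILC model. As written, that model cannot estimate whether countermeasure effectiveness differs by age or marker; this follows from its terms and needs no numerical assumption. That its marker coefficient mixes vulnerability with response is conditional on marker effects that differ between nights. In that case an IRR of 2.0 confined to the placebo night or to the coffee night appears as about 1.26 under the assumed overdispersion. Detection of the placebo-only marker falls from about 65% to 19–23%, and a coffee-only IRR of 2 to 3 is flagged as a general type effect in 18–37% of trials, against 7–9% under the null. ILC rates, dispersion and marker frequency are all assumed.

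The consequence is confined to secondary objectives and to the marker claim under Expected results. The overall comparison of blue light, coffee and placebo is not affected. The correction is worth making because it is specific and cheap.

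**What to change.** In Analyses of variables, add age-by-treatment and type-by-treatment terms to the negative binomial model for ILC, and name the contrasts:

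- Effectiveness: marker (or age) × (blue light − placebo) and marker (or age) × (coffee − placebo), reported as ratios of IRRs with confidence intervals.
- Impairment: the marker contrast on the placebo night, described as the night without an active countermeasure, with the notes that the drink contains 15 mg of caffeine and that no rested drive is available, so the contrast shows level and not change.

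Take the same contrasts from the existing ANOVA models; their terms need no change. The overall treatment IRRs can stay on the model without interactions, because once interactions are added a treatment coefficient refers to the reference group only.

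The cost is wording, with no new data, visits or participants. The price in precision arises when the marker acts equally on all nights: the placebo-night standard error is then about 12–37% larger than that of the three-night mean (assumed correlation 0.7 to 0.3). The 48 participants were not sized for interaction contrasts, so these should be presented as estimates with intervals.

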**Study design**

Experimental design

This is an interventional study: Double-blind (except for blue-light), Randomized, Crossover, Comparative versus referent countermeasure of sleepiness: coffee (2*200 mg of caffeine) and placebo.

The study is divided into the following periods:

1. **selection period** without treatment between selection and inclusion visits to check the absence of exclusion criteria with questionnaires, polygraphic recording (respiratory sleep disorders and periodic leg movements) and actimetry (sleep efficiency, total sleep time)
2. **acute treatment period**, each volunteer will be randomly allocated to successively and randomly receive either continuous blue light exposure or 2*200 mg of caffeine or placebo of caffeine during night driving with at least 1 week between treatment.

Experimental protocol

SELECTION

Participant will complete the French version of the Basic Nordic Sleep Questionnaire (BNSQ), the self-report symptoms inventory SCL-90R, the chronotype questionnaire of Horne and Ostberg, the Epworth sleepiness scale. They will to have 7 consecutive days monitoring using actimeters and 1 night using polygraph.

INCLUSION

Participants will be screened for eligibility criteria. They will sign informed consent, perform cognitive tests, complete the caffeine sensitivity questionnaire. Blood samples will be collected.

DRIVING SESSION

Each subject, will come at the laboratory at 9:30 PM, and will kept awake until the time of the experimental session.

For each driving session (Blue light, caffeine and placebo of caffeine), all participants will drive 400 km (250 miles) on the same 2-lane highway for 4 hours. After 2 hours of driving (200 km, 125 miles) subjects will take a 15-minutes break. The night-time driving session will start at 1:00 AM and Stop at 5:15 AM. At the beginning, middle and end of the driving, participants will be asked to rate their instantaneous fatigue and sleepiness. After driving, sleep recuperation will be recorded in laboratory during a minimum of 6h. Saliva will be collected before and after the driving session and after sleep recuperation.

The subjects were instructed to maintain a regular sleep-wake schedule and were monitored by actimetry during the 3 days preceding each experimental session and during the 3 days after each experimental session.

**
[figure not shown]
**

C: Coffee

P: Placebo

BL: Blue Light

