**Criteria of assessment**

Primary efficacy criterion

- Number of inappropriate line crossings (ILC) identified from the video recordings.

Secondary efficacy criteria

- Standard deviation of the position of the car
- Self-rated sleepiness during driving
- Self-rated fatigue during driving
- Sleep latency during the subsequent sleep
- Sleep efficiency during the subsequent sleep
- Time course of EEG slow wave activity during the subsequent sleep

Secondary criteria

- Chronotype
- Caffeine sensitivity
- Habitual sleep patterns
- PER3 polymorphism
- COMT polymorphism
- ADORA2A polymorphism
- Reaction time and percentage of errors at cognitive tests
- Saliva cortisol concentration before and after the driving session and after the sleep recovery.
- Saliva amylase concentration before and after the driving session and after the sleep recovery.

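### The deciding comparison for the primary endpoint is not named consistently; if either blue-light contrast may count as success, the 5% error can reach about 9% at worst

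*Protocol*

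**What the plan says.** There is a single primary criterion (Protocol, Criteria of assessment): "Number of inappropriate line crossings (ILC) identified from the video recordings". The design is "Randomized, Crossover, Comparative versus referent countermeasure of sleepiness", and each man drives once under blue light, coffee and placebo. Four sections bear on which comparison of this endpoint decides the trial.

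- **Study objectives, primary objective:** its opening words are "To compare the effects of continuous blue light exposure during driving with those of coffee (2*200 mg of caffeine) and coffee placebo". This is two contrasts, blue light versus coffee and blue light versus placebo.
- **Statistical considerations, sample size:** the aim is "demonstrating a slight difference between the 2 countermeasures (coffee and blue light) with a power of 90 % and a type-I error =5" percent. This is one contrast, framed as a difference.
- **Analyses of variables, primary efficacy variable:** a negative binomial model with a three-level treatment factor, clustered on participant. On reporting: "We reported comparisons of ILC between treatments as incidence rate ratios (IRR) with 95% confi­dence intervals (CI". No order, overall test or adjustment is given.
- **Expected results:** the first item reads "Improvement of nocturnal driving ability with countermeasures to sleepiness (coffee and continue blue light exposure) versus placebo in young and middle-aged healthy volunteers". The next item expects blue light to help as much as coffee.

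**The concern.** The sections cannot all describe the same primary test. If blue light versus coffee alone decides, as the sample size text suggests, the sponsor expects the deciding test to show no difference. If superiority over placebo decides, as the expected results suggest, the sample size section gives that contrast no error rate and no power. If both blue-light contrasts decide, as the objective suggests, nothing says whether one is enough or both are needed.

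The contrasts can disagree. Blue light may beat placebo without differing from coffee, or may differ from coffee without a clear result against placebo. The protocol does not say which of these outcomes meets the primary objective. If that is settled after the data are seen, the stated 5% no longer describes the primary claim. The Background section says the purpose is to know what to advise drivers, so a false claim for blue light would have practical consequences.

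**Working it through.** **1. The plan's own figure.** The inputs are "Effect size f = 0.3", "α err prob = 0.05", power 0.90 and a total of 48, all from the sample size section. The G*Power test is not named.

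- Three-level overall F test, sessions treated as independent: noncentrality = f² × N = 0.09 × 144 = 12.96 on 2 and 141 df, power 0.901. The smallest balanced N is 144 sessions, and 144 / 3 = 48. This matches exactly.
- Two-level within-subject F test, closer to the wording: 61–62 subjects at correlation 0, 43–44 at 0.3 and 32 at 0.5. It gives 48 only at some correlation between 0 and 0.3, and none is stated.
- Paired t test: 48 needs a standardised difference of about 0.48, which is not stated either.

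The 48 therefore reproduces, but most directly from an overall three-condition test and not from the two-countermeasure contrast in the text. Because the test is unnamed, this is an inference. It shows that the protocol should say which test its 5% and 90% belong to.

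**2. Family-wise error when all three conditions are equal.** Assumptions: each contrast is tested two-sided at 5% (matching the 95% intervals; sidedness is not stated), equal variances and equal within-man correlations, and a normal approximation.

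- Blue light minus coffee and blue light minus placebo share one condition. In units of the residual variance, each has variance 2 and their covariance is 1, so their correlation is 1/2.
- Two blue-light contrasts: P(either) = 0.05 + 0.05 − P(both). Simulation with 2 million draws gives P(both) = 0.0092, so P(either) = 0.10 − 0.0092 = 0.0908, about 9.1%. If the contrasts were independent it would be 1 − 0.95² = 9.75%.
- At least one of the two falsely favouring blue light: about 4.5%, against 2.5% for a single contrast.
- All three pairwise contrasts: the range of three means exceeds 1.96 × √2 = 2.77 with probability 12.2%. If independent, 1 − 0.95³ = 14.3%.

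**3. When the conditions are not all equal.** If coffee differs from placebo, blue light can equal at most one of them. At most one pairwise null hypothesis is then true, and the family-wise error is at most 5% with no adjustment. The figures in step 2 are therefore maxima.

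**4. Rules that could be written down, all three conditions equal.**

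| Rule | Family-wise error |
|---|---|
| Either blue-light contrast counts | 9.1% |
| Any of three contrasts counts | 12.2% |
| One named contrast | 5.0% |
| Pairwise tests only after a significant 2-df treatment test | 5.0% |
| Both blue-light contrasts required | 0.9% |
| Bonferroni, two / three contrasts | 4.6% / 4.4% |

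The gate is a closed test. With three conditions, any two pairwise nulls together imply that all three are equal, and the 2-df test addresses exactly that hypothesis.

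**5. What splitting alpha would cost.** A paired contrast with exactly 90% power at 48 men (standardised difference about 0.478) falls to about 84% at alpha 0.025 and about 79% at 0.0167. This is illustrative, on a normal scale and not in the negative binomial model. The gate and a fixed order both avoid the split.

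**The case against.** The sample size section does single out coffee versus blue light and attaches the 5% to it. If that contrast alone is primary, its error is 5%. A reader might infer that the protocol names no deciding comparison at all; that goes too far. What stands against the objection is that the primary objective adds the placebo contrast, and the expected results predict no difference on the very contrast the trial is said to be sized to detect.

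A reader might also take 9–12% as the actual error rate. The documents do not support that. It needs all three conditions to be equal, whereas the Background and Clinical assessment methods sections cite evidence that coffee and similar countermeasures work. It also needs a rule that any one significant contrast suffices, which the protocol never states, though it does not exclude it. Coffee versus placebo is not in the primary objective, so 12% is not the rate for that objective.

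A further temptation is to multiply the contrasts by the two age groups, because the expected results mention both. The effect of age is a secondary objective, age enters the primary model as a determinant, and no separate age-group models are specified. Age-group multiplicity should not be counted.

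Finally, a statistical analysis plan that is not shown could hold a gate or adjustment, so its absence from the protocol is not by itself a fault. Such a plan would still leave the objective, sample size and expected results in disagreement.

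**Conclusion.** The concern holds as an inconsistency in the protocol's own text: for one endpoint, its sections point to different deciding comparisons. The possible inflation is from 5% to about 9% for the two blue-light contrasts, or to about 12% if coffee versus placebo is also counted. Both are worst cases that assume three equal conditions, two-sided 5% tests and success on any one contrast. If coffee really differs from placebo, the rate is at most 5%. The lasting problem is less the size of the inflation than that the criterion for success could be chosen after the results are known. It is worth correcting because the correction is simple and nearly free.

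**What to change.** In the primary efficacy analysis, adopt one of these rules:

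- **Gate:** interpret the pairwise incidence rate ratios only if the 2-df treatment test in the planned negative binomial model is significant at 5%; each pairwise test is then at 5%. If the Wilcoxon fallback is used, the gate needs a matching overall rank test, such as Friedman's.
- **Fixed order:** state one order for the two blue-light contrasts, each at two-sided 5%, with the second tested only if the first is significant. The order matters. With coffee first, and blue light truly equal to coffee as the sponsor expects, the placebo contrast would be reached only about 5% of the time. With placebo first, the leading test is one for which no power is stated.

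Label coffee versus placebo as supportive. Make the primary objective, sample size section and expected results agree on the deciding comparison, and say which test the 5% and 90% refer to. State that a non-significant blue light versus coffee difference will not be reported as showing the same effect.

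The cost is a few sentences, with no added participants, data or model and no split of alpha. The downside is small: no pairwise claim can be made if the gate fails, and the second contrast cannot be claimed if the first in the order fails.

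### Lateral position is planned as an ordinary two-way ANOVA although each participant drives under all three treatments; sleep latency and efficiency are given a time factor they do not have

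*Protocol*

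**What the plan says.** The protocol's Study design section describes the trial as "Randomized, Crossover, Comparative versus referent countermeasure of sleepiness", and adds: "For each driving session (Blue light, caffeine and placebo of caffeine), all participants will drive 400 km". Each participant therefore contributes three lateral-position values.

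The section Analyses of variables then plans the secondary outcomes in three sentences:

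- Lateral position: "The standard deviation of the position of the car will be compared by a two-way analysis of variance (ANOVA", with age by treatment, genotype by treatment and similar pairs as factors.
- Sleepiness and fatigue: "Subjective sleepiness or subjective fatigue will be compared by a three-way analysis of variance for repeated measurements (rANOVA", with time as the third factor.
- Recovery sleep: "Sleep latency, sleep efficiency or sleep EEG power density will be compared by a three-way analysis of variance for repeated measurements (rANOVA", again with time as the third factor.

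The primary model in the same section, a negative binomial regression, is clustered by participant. Among the secondary efficacy criteria, latency is defined as "Sleep latency during the subsequent sleep" and efficiency is defined for the same sleep. Only EEG slow-wave activity is defined as a time course.

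**The concern.** In a crossover, the three drives of one person are correlated. An ordinary two-way ANOVA has a single residual that mixes differences between people with differences between drives of the same person. That residual is too small for comparing groups of people (age, genotype, cognitive or hormonal type) and too large for comparing treatments. The first error produces false marker findings. The second hides treatment effects and treatment-by-marker interactions. Both touch stated secondary objectives, because the protocol wants to characterise who is impaired by sleep loss and who benefits from a countermeasure.

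The recovery-sleep sentence has a different fault. It puts three outcomes under one model with a time factor, and two of them are measured once per session.

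**Working it through.** **Inputs from the protocol.** 48 participants (24 young, 24 middle-aged), 3 sessions each, so 48 × 3 = 144 values; α = 0.05; f = 0.3; power 0.90.

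**Assumptions, not in the protocol.** The correlation ρ between two drives of the same person is taken as 0.3, 0.5 and 0.7, equal for all pairs of sessions, with total variance 1 and complete data.

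**The plan's own figure.** With noncentrality λ = f² × N = 0.09 × 144 = 12.96 on 2 and 138 df, power is 0.901. So 144 independent values, or 48 participants × 3 sessions, reproduces the stated 48. A repeated-measures test with ρ = 0 gives 0.897 at 48. The protocol does not name the test used, so this is background only.

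**Expected mean squares with no true effects.**

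- Between participants (46 df, also the expectation for age): 1 + 2ρ
- Within participants (92 df, also the expectation for treatment and age by treatment): 1 − ρ
- Ordinary two-way residual (138 df): [46(1 + 2ρ) + 92(1 − ρ)] / 138 = 138/138 = 1

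The ordinary F for age is therefore inflated by 1 + 2ρ, and the ordinary F for treatment and for the interaction is shrunk by 1 − ρ. At ρ = 0.5 the factors are 2.0 and 0.5. The critical value for age is F(1,138) = 3.91, so a correctly scaled statistic needs to reach only about 3.91/2.0 = 1.95. The critical value for treatment is F(2,138) = 3.06, so a correctly scaled statistic must reach about 3.06/0.5 = 6.12.

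**True size of the nominal 5% tests, by simulation.**

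| ρ | F factor, age | Size, age main effect | F factor, treatment | Size, treatment and age by treatment |
|---|---|---|---|---|
| 0.3 | 1.6 | 12% | 0.7 | 1.5% |
| 0.5 | 2.0 | 16 to 17% | 0.5 | 0.3% |
| 0.7 | 2.4 | 21% | 0.3 | 0.01% |

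With the participant in the error structure (46 df for age, 92 df for the others), all three tests return to about 5%. At ρ = 0 the two analyses agree.

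**Power for the treatment test.** Under the correct model λ = 144f²/(1 − ρ). Two effects are compared. The first is one arm shifted by 0.45 SD, which is an assumption: the arm means 0, 0, 0.45 have variance (0.15² + 0.15² + 0.30²)/3 = 0.045, so f = √0.045 ≈ 0.21. The second is the protocol's f = 0.3, read on the total-SD scale.

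| ρ | f ≈ 0.21, ordinary | f ≈ 0.21, repeated measures | f = 0.3, ordinary | f = 0.3, repeated measures |
|---|---|---|---|---|
| 0.3 | 60% | 77% | 93% | 97% |
| 0.5 | 60% | 90% | 95% | over 99% |
| 0.7 | 60% | 99% | 98% | 100% |

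**The time factor, outcome by outcome.** Sleepiness and fatigue have three ratings per session: "At the beginning, middle and end of the driving, participants will be asked to rate their instantaneous fatigue and sleepiness". EEG slow-wave activity is a time course by definition. For latency and efficiency there is one recording per session: "After driving, sleep recuperation will be recorded in laboratory during a minimum of 6h". One value per session gives time a single level, so neither its main effect nor any interaction with it can be estimated.

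**The case against.** The strongest defence is that the protocol never states independence. It names factors, not error terms, and two-way ANOVA is common shorthand even when one factor is within-subject. The repeated-measures label appears only where time is listed, so its absence for lateral position may mean only that there is no time factor. The clustered primary model shows that the authors knew the sessions were paired, and a statistical analysis plan that is not shown could settle the matter. This stands as far as intent is concerned: one cannot claim that the analysis will be run wrongly. It does not rescue the text. Beside two sentences that do say repeated measurements, the natural reading of the lateral-position sentence is the ordinary ANOVA.

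Three stronger readings are tempting, and the documents do not support them.

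- A reader might infer that sleep latency and efficiency also have wrong error terms. They do not: their plan is already a repeated-measures ANOVA. If the single-level time factor is dropped, age by treatment remains, with treatment as the repeated factor.
- A reader might infer that the age objective is exposed to false positives. That objective concerns the effect of age on how well the countermeasures work, which is the age-by-treatment interaction, and that test becomes conservative. The inflation concerns main effects of age and markers.
- A reader might infer a large loss of power at the planned effect. At f = 0.3 the ordinary ANOVA stays above 90%. The larger loss appears at a smaller effect that the protocol does not state.

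It could also be said that time means parts of the night, or the actimetry days after each session. The protocol defines no such intervals for latency or efficiency, and its criteria name only the one subsequent sleep.

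**Conclusion.** The point holds for lateral position as written: the planned test omits the participant from its error term in a three-session crossover. Between-participant main effects are tested too liberally, and treatment and interaction effects too conservatively. The sizes in the tables rest on the assumed correlations of 0.3 to 0.7. A correlation of zero would remove the problem, but it is hard to square with the protocol's own background, which stresses wide differences between individuals at night. For genotype and other types the direction is the same as for age, and the amount depends on group sizes.

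For sleep latency and efficiency the fault is limited to a factor that cannot be estimated.

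The weight is moderate. The primary analysis allows for clustering by participant and is untouched, and the lateral-position error does not favour a false claim that a treatment works. It does affect the second outcome measure and the search for markers of vulnerability.

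**What to change.** Change two sentences in Analyses of variables.

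1. For lateral position, state that treatment is a within-participant factor. A repeated-measures ANOVA is enough. A linear mixed model with a random participant effect and fixed effects for treatment, age (or marker) and their interaction, preferably with session number, does the same and can keep participants who miss a session.
2. For sleep latency and sleep efficiency, use that same age (or marker) by treatment repeated-measures model without time. Keep the time factor only for sleepiness, fatigue and EEG slow-wave activity.

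The cost is wording only: no new data, no more participants and no change to the primary analysis. The change should be made before the data are analysed.
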